### Trial Design and Settings

A quasi-experimental study of the type before and after, with a single arm, will be conducted with all nurses from inpatient units of a tertiary-level university hospital in the interior of the southeast of São Paulo to implement a training program to assess the risk of early clinical deterioration. This study aims to demonstrate causality between the proposed intervention and the nurses’ ability to use the NEWS2 tool to assess the patient’s clinical deterioration and provide appropriate referrals. Quasi-experimental designs are often used when assigning participants randomly to different groups is not feasible or ethical. This allows for intragroup comparison of outcomes (ie, comparing the pretraining and posttraining results in the same group). In this study, having only a subset of the staff receiving the training would not be feasible. Although a quasi-experimental design does not offer the same level of control as a randomized controlled trial, it can provide valuable insights into the effects of the training program because it offers a real-world evaluation of the intervention’s impact within the specific setting and considers the practical constraints of implementation.

The trial was registered in the Brazilian Registry of Clinical Trials (ReBEC) with the number RBR-5hq9y3k. For the design of the method, the limits of the Guideline for Reporting Evidence-Based Practice Educational Interventions and Teaching (GREET) [11] were respected.

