### Sample Size and Sampling

The minimum sample size was calculated according to the stages of data collection in the pretest and posttest. To evaluate the responsiveness of part 1 of the RRT survey comparing the scores from the two evaluation periods, a paired student *t* test was used. In this calculation, a significance level of 5% was assumed with a test power of 80% and an effect size of 0.50, which, according to Cohen [17], can be considered an effect size of medium degree. The calculation resulted in a minimum sample of 34 participants. To carry out this sample calculation, G*Power 3.1.9.2 software was used [18,19].

To assess the internal consistency of part 2 of the RRT survey, we referred to the recommendation proposed by the COSMIN (Consensus-Based Standards for the Selection of Health Measurement Instruments) initiative that at least 50 participants are necessary for a sample to be considered adequate when this measurement property is evaluated [20].

To evaluate assertiveness in filling out the NEWS2 before and after the intervention, the same methodology was proposed by the COSMIN initiative that at least 50 participants are necessary [20]. Thus, 50 participants will be included in the study to meet all the proposed objectives.

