### Data Collection

The experiment will be offered from July to December 2023 and include nurses who work in the clinical and surgical floor units.

Initially, a meeting will be held with the managers of the inpatient units to present the training program. Then, nurses will be recruited through an individual invitation to be offered by the researcher in the work units. After acceptance by the participants, a roster will be set up, together with the managers of the units, to assist in the organization of work rosters so that every position is covered when the nurses leave to participate in the training. Several training sessions will be made available in the morning, afternoon, and evening to carry out the training within the working hours of each nurse and according to what was described in the JITT method. The training sessions are structured to be 1 hour long and include the following steps: training presentation, signing of the informed consent form, application of the pretest, training, application of the posttest, and final evaluation. All nurses will participate in a single session and receive a participation certificate after completing all the steps described. The training will be carried out in a training room within the hospital.

Content analysis will be carried out during the qualitative phase (focal group). The most appropriate contents and strategies for nurses, as defined by them, will be combined to determine the elements of the intervention. Regarding the web-based questionnaire and the RRT survey, both of which are quantitative instruments, any increase in the score from the pretest to posttest will represent an improvement and, consequently, indicate the effectiveness of the intervention.

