### Statistical Analysis

Qualitative variables will be described by calculating frequencies and percentages, and quantitative variables through position measurements and dispersion.

Comparisons between the two time periods concerning the score of the NEWS2 instrument and part 1 of the RRT survey instrument will be carried out using paired Student *t* tests or paired Wilcoxon tests [21], according to the data distribution. The distribution of data will be evaluated using the Shapiro-Wilk test.

The internal consistency of part 2 of the RRT survey instrument will be assessed using Cronbach α coefficient [22]. This coefficient ranges from 0 to 1, where values >.7 indicate that the measurements are reliable [23].

The statistical software SAS and SPSS (version 28; IBM Corp) will be used to carry out the analysis with a significance level of 5%.

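### The Data Collection section treats any pre-to-post score rise as showing effectiveness, which bypasses the planned 5% paired test and is met about half the time by chance

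*Protocol article*

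**What the plan says.** The protocol article gives two criteria for judging the pre-to-post change.

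- **Data Collection.** The sentence opens "Regarding the web-based questionnaire and the RRT survey, both of which are quantitative instruments" and continues that "any increase in the score from the pretest to posttest will represent an improvement and, consequently, indicate the effectiveness of the intervention". It mentions no test, significance level or interval.
- **Statistical Analysis.** "Comparisons between the two time periods concerning the score of the NEWS2 instrument and part 1 of the RRT survey instrument" are to be made with paired t or paired Wilcoxon tests, depending on the distribution, at a 5% significance level. Part 2 of the RRT survey is given only a Cronbach α.

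The sample size rests on the second criterion. For the paired t test on RRT part 1, "a significance level of 5% was assumed with a test power of 80% and an effect size of 0.50". The article then says "The calculation resulted in a minimum sample of 34 participants" and, after considering internal consistency and NEWS2, "Thus, 50 participants will be included in the study to meet all the proposed objectives".

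Nothing in the article links the two criteria or says which one governs.

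**The concern.** An increase of any size is a threshold of zero, and the sentence attaches the study's conclusion to that threshold. Sampling error alone will move a mean up or down. A rule that accepts every upward movement therefore has none of the error control that the rest of the plan provides.

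On RRT part 1 the two criteria can give opposite answers from the same data: a small, non-significant gain is effective under Data Collection and not shown under Statistical Analysis. For the web-based questionnaire there is no second criterion to fall back on, because Statistical Analysis names no test for a score under that name. At stake is the main claim of the study, since Trial Design and Settings says the aim is to demonstrate causality.

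**Working it through.** **Inputs from the article.** Significance level 5%, power 80%, standardised effect 0.50, minimum n = 34, planned n = 50 (Sample Size and Sampling); paired t or Wilcoxon test at 5% (Statistical Analysis); the any-increase rule (Data Collection). Sidedness is not stated.

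**Step 1: reproduce the article's figure.** The power of a two-sided paired t test is P(|T| > t(0.975, n−1)), where T is noncentral t with n−1 degrees of freedom and noncentrality 0.50 × √n. The smallest n with power of at least 0.80 is 34, with power 0.808. This matches the article exactly. A one-sided test would give 27 and the two-sided normal approximation 32. The plan's test is therefore taken as two-sided. At n = 50 its power for the same effect is 0.934.

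**Step 2: error rate of the any-increase rule.** Suppose there is no true change and the change scores are symmetric about zero. The mean change is then also symmetric about zero, so P(mean change > 0) = 0.50 whatever the sample size. The simulation used 100,000 trials per row:

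| n | Mean rises at all | Significant rise (two-sided 5% test) | Significant in either direction |
|---|---|---|---|
| 34 | 0.501 | 0.025 | 0.050 |
| 50 | 0.500 | 0.025 | 0.049 |

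Exact ties lower the first figure slightly. With integer change scores at n = 50 and an assumed standard deviation of 0.5, 1 or 2 points before rounding, the rule is met with probability 0.451, 0.473 or 0.487.

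The ratio to the planned test is 50/5 = 10 against the two-sided level, or 50/2.5 = 20 against the favourable direction.

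**Step 3: size of the gap between the criteria.** The smallest mean gain that reaches significance, in standard deviations of the change, is t(0.975, n−1)/√n. This is 0.35 at n = 34 and 0.28 at n = 50. Any observed gain between zero and that value counts as effective under one section and not under the other.

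**Step 4: more than one score.** The article does not say how scores combine. With correlation ρ between two changes, both rise by chance with probability 1/4 + arcsin(ρ)/(2π), and at least one rises with probability 1 minus that. For ρ = 0, 0.5 and 0.8, at least one rises with probability 75%, 67% and 60%, and both rise with probability 25%, 33% and 40%.

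**Step 5: a shift not due to training.** Assume a pure retest gain of d standard deviations of the change at n = 50. The rule is met with probability Φ(d√50), and the paired test's rate comes from the noncentral t.

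| Assumed d | Any increase | Two-sided paired test significant |
|---|---|---|
| 0.1 | 76% | 11% |
| 0.2 | 92% | 28% |
| 0.3 | 98% | 55% |

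**The case against.** The best defence is that the sentence states only the direction of scoring. It sits in Data Collection, next to a remark on content analysis, while the inferential rule is in Statistical Analysis and the sample size follows that rule. Read together, the two would mean that higher is better, as judged by the paired test. That may be what was intended. The sentence goes further, however: it accepts an increase of any size and draws effectiveness from it. If only direction was meant, the correction is just as short.

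It is also fair that the sentence does not say whether the score is each nurse's or the group mean. The 50% figure is for a group mean.

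A reader might infer more than the article supports:

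- **That an increase is said to prove effectiveness.** The word used is weaker: indicate.
- **That the whole analysis is contradicted.** The two sections overlap only on RRT part 1.
- **That parts 2 and 3 of the RRT survey are judged by this rule.** Statistical Analysis limits the before-after comparison to part 1. As Preintervention Assessment describes it, part 3 collects background information and would give no change score.
- **That the false-positive rate is 75%.** That needs a rule that either score suffices, which the article does not state. It also needs independence, which is implausible for scores from the same nurses.
- **That retest gains are a fault of this sentence alone.** The shifts in Step 5 are assumed, and the paired test is affected too.
- **That NEWS2 should be tested only after RRT part 1.** The article does not rank the two. Its stated aim concerns the ability to use NEWS2, and NEWS2 is one of the reasons given for n = 50.

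**Conclusion.** The point stands in limited form. Taken literally, the Data Collection sentence gives about a 50% chance of declaring effectiveness on one mean score when nothing has changed. The planned test gives 5% two-sided, or 2.5% in the favourable direction. The figure assumes a group mean and a symmetric no-change distribution, does not depend on sample size, and falls to 45 to 49% under the integer-score assumptions shown.

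The conflict is direct for RRT part 1. For the web-based questionnaire the problem is that no other criterion is stated under that name. The sample size calculation and the choice of paired tests are not in question.

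**What to change.** Replace the sentence in Data Collection with wording such as:

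> A higher score is the favourable direction. Improvement will be concluded only if the pre-post change is in that direction and the paired t or Wilcoxon test described under Statistical Analysis is significant at the two-sided 5% level. The mean (or median) change and its 95% confidence interval will be reported.

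If the web-based questionnaire score is used to judge effectiveness, add it to the scores tested under Statistical Analysis. Neither NEWS2 nor RRT part 1 needs to be ranked below the other, and the Wilcoxon option stays.

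The cost is one or two sentences. No participants are added: power at the design effect is 93% with the planned 50. Success becomes harder to show, since at n = 50 a mean gain must reach about 0.28 standard deviations of the change when the t test is used.

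The test restores control of sampling error only. In a single-arm study with pretest and posttest in the same one-hour session, a significant rise may still include a retest effect. That is why the proposed wording concludes improvement and not effectiveness.

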### Data Management

The gathered data will be compiled in a spreadsheet using Excel 2010 (Microsoft Corporation) using double entry. In this spreadsheet, numerical encodings will be created for categorical variables. Quantitative variables will be inserted as collected. To avoid erroneous double entries or differences in the created codes, preset values for categorical variables will be used. The spreadsheet containing the data will be password-protected and solely accessible by the lead investigator.

### Data Analysis

The data spreadsheet will be imported into SAS 9.4 software (SAS Institute). The results of the focus groups, as well as the preintervention and postintervention assessment questionnaires, will be submitted for content analysis.

### Statistical Analysis

Qualitative variables will be described by calculating frequencies and percentages, and quantitative variables through position measurements and dispersion.

Comparisons between the two time periods concerning the score of the NEWS2 instrument and part 1 of the RRT survey instrument will be carried out using paired Student *t* tests or paired Wilcoxon tests [21], according to the data distribution. The distribution of data will be evaluated using the Shapiro-Wilk test.

The internal consistency of part 2 of the RRT survey instrument will be assessed using Cronbach α coefficient [22]. This coefficient ranges from 0 to 1, where values >.7 indicate that the measurements are reliable [23].

The statistical software SAS and SPSS (version 28; IBM Corp) will be used to carry out the analysis with a significance level of 5%.

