### Outcomes

A form for analyzing the sociodemographic profile will be applied to nurses with the following variables: age, sex, education level, time of training, place, and time of work in the unit.

The effect of evaluating the theoretical content related to the early assessment of clinical deterioration by each participating nurse will be considered to compare the pretraining and posttraining results.

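### Effectiveness is to be inferred from any rise in score, a rule not tied to the 5% tests, and no outcome is labelled primary

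*Protocol article*

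**What the plan says.** All references are to the protocol article.

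- **Data Collection** sets the success rule. It opens with "Regarding the web-based questionnaire and the RRT survey, both of which are quantitative instruments", and continues that "any increase in the score from the pretest to posttest will represent an improvement and, consequently, indicate the effectiveness of the intervention". No test is mentioned. The sentence does not say whether one instrument is enough or both must rise, and NEWS2 is not in it.
- **Statistical Analysis** plans "Comparisons between the two time periods concerning the score of the NEWS2 instrument and part 1 of the RRT survey instrument", by "paired Student *t* tests or paired Wilcoxon tests [21], according to the data distribution", with a significance level of 5%. No ranking of the two scores is given.
- **Outcomes** labels nothing as primary. Its one effect statement is "The effect of evaluating the theoretical content related to the early assessment of clinical deterioration by each participating nurse will be considered", for a comparison of pretraining and posttraining results.
- **Sample Size and Sampling** has one power calculation, "To evaluate the responsiveness of part 1 of the RRT survey comparing the scores from the two evaluation periods": effect size 0.50, 5% level, 80% power, 34 participants. NEWS2 is sized only by a rule of at least 50 participants taken from a measurement-property standard. The study will include 50.
- **Trial Design and Settings** states the causal aim as nurses' ability to use NEWS2 and to refer appropriately.
- **Postintervention Assessment** assigns the evaluation of effectiveness to the RRT survey.

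**The concern.** The article contains two decision rules that do not meet. One is a pair of hypothesis tests at 5%. The other declares effectiveness from the direction of change alone. If the second is followed, a rise too small to distinguish from chance counts as proof, and the 5% level has no part in the conclusion.

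The missing primary label makes this worse. The aim points to NEWS2, the effectiveness evaluation to the RRT survey, the power calculation to RRT part 1, the success rule to the web-based questionnaire and RRT survey, and the tests to NEWS2 and RRT part 1. If the scores disagree, the text would support presenting either as the main result.

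**Working it through.** **Inputs from the article:** 5% level, 80% power, effect size 0.50 (paired), minimum 34 participants, planned 50, two scores tested. **Assumption:** the correlation ρ between the changes in two scores. The article gives none, so a range is shown. Both scores come from the same nurses, so positive values are likely.

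**1. The plan's own figure.** Power of a paired t test from the noncentral t distribution, with n − 1 degrees of freedom and noncentrality 0.50 × √n. At two-sided 5% the smallest n with at least 80% power is 34 (power 0.808). One-sided it would be 27. The stated 34 is reproduced, and the design is in effect two-sided. At n = 50 the power is 0.934.

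**2. The success rule read literally.** With no true change and a roughly symmetric mean change, one mean rises with probability 0.5. For two instruments the probability that both rise is 1/4 + arcsin(ρ)/(2π), which by symmetry is also the probability that neither rises. At least one therefore rises with probability 1 − [1/4 + arcsin(ρ)/(2π)].

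| Assumed ρ | At least one rises | Both rise |
|---|---|---|
| 0 | 1 − 0.250 = 0.750 | 0.250 |
| 0.5 | 1 − (0.250 + 0.083) = 0.667 | 0.333 |
| 0.8 | 1 − (0.250 + 0.148) = 0.602 | 0.398 |

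A simulation at n = 50 gave 0.755, 0.667 and 0.602 for at least one rise. Even if both had to rise, the chance of a false claim would be 25% to 40%.

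**3. If a significant result on either tested score were taken as effectiveness.** The text neither states nor excludes this. For two two-sided 5% tests, the chance of at least one false positive if independent is 1 − 0.95² = 0.0975. From the bivariate normal distribution:

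| Assumed ρ | Either direction | False increase only (nominal 0.025) |
|---|---|---|
| 0 | 0.0975 | 0.0494 |
| 0.3 | 0.0951 | 0.0476 |
| 0.5 | 0.0907 | 0.0454 |
| 0.8 | 0.0781 | 0.0390 |

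The limit at ρ = 1 is 0.05. Simulated paired t tests at n = 50 gave 0.100, 0.090 and 0.078 at ρ = 0, 0.5 and 0.8 (either direction). If both scores had to be significant, there would be no inflation.

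**4. After repair.**
- One primary score at two-sided 5%: 34 participants still suffice, and 50 give 93.4% power at effect size 0.50.
- Two co-equal scores with Bonferroni at 2.5% each: familywise error is at most 5%, 41 participants are needed for 80% power, and 50 give 88.5% power per score at effect size 0.50. Holm is at least as powerful.

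**The case against.** The kindest reading of the Data Collection sentence is that it only fixes the scoring direction: higher is better. Its first half can be read that way. Its second half cannot, because it goes on to draw effectiveness as a consequence of the rise.

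A second defence is that the main measure can be worked out. Outcomes speaks of theoretical content, Preintervention Assessment ties that to the RRT survey questionnaire, Postintervention Assessment gives that survey the effectiveness question, and only RRT part 1 is powered. This has weight and is why RRT part 1 is the natural primary. It does not settle the matter, because Trial Design and Settings states the aim in terms of NEWS2.

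Some stronger readings are tempting but unsupported:

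- *The false-claim rate is almost doubled.* The 9.75% requires independent scores and a rule that either one suffices. The article gives no correlation and no such rule.
- *A significant NEWS2 result alone proves effectiveness.* The success rule does not name NEWS2.
- *Three tests give 1 − 0.95³ = 14.3%.* No test is planned for the web-based questionnaire. Statistical Analysis tests two scores only, and Data Analysis sends the assessment questionnaires to content analysis.
- *The absence of a multiplicity adjustment is itself an error.* A condensed article may leave that to an analysis plan that is not shown.

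**Conclusion.** The point holds as a fault in what the article states, not as a missing multiplicity adjustment. Applied literally, the any-increase rule gives about a 50% chance of a false claim per instrument, and 60% to 75% for at least one of two (assumed correlation 0.8 to 0). These figures assume no true change, a symmetric mean change, negligible probability of a change of exactly zero, and no gain from simply answering the same items twice.

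The mismatch between aim, powered score, tested scores and deciding instruments is a second fault of the text. The familywise range of about 7.8% to 9.75% (same correlations) is conditional on an either-score rule that the article does not state.

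The sample size of 34, and the planned 50, are not affected. The point should be corrected before analysis, but it does not threaten feasibility.

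**What to change.** - **Data Collection:** replace the any-increase rule with a statement that effectiveness will be concluded only from a statistically significant increase on the prespecified primary test. Higher scores meaning improvement can stay as a note on scoring direction.
- **Outcomes and Statistical Analysis:** name the pre-post change in RRT survey part 1 as the primary outcome, tested two-sided at 5%, with the NEWS2 score as secondary. State the role of the web-based questionnaire.
- **Alternative:** if the sponsor wants NEWS2 to count equally because the stated aim is framed around it, declare the two scores co-primary with either one sufficient, and apply Holm or Bonferroni across them.

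The cost is a few sentences and no extra participants: 50 give 93.4% power for a single primary, or at least 88.5% per score for two, at effect size 0.50. The downside is small. A rise without significance could no longer be called proof of effectiveness, and neither could a NEWS2 result alone under the primary and secondary option.
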